### Sample size

'Need for recovery after work' is the primary outcome of this study and was therefore used for the power calculation. The 'need for recovery after work' scale comprises 11 dichotomized items [26]. Based on previous findings [12,27] the expected effect size is 0.40. To detect this effect size (assuming a two-sided significance level: 0.05, power (1-β): 80%) 63 persons per group are needed. Taking into account 20% loss to follow up, the required sample size is 160 persons in total, with 80 participants assigned to the control group and 80 participants to the intervention group.

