### Outcome measures

#### Primary outcome measure

##### 'Need for recovery after work'

Primary outcome is defined as the 'Need for Recovery (NFR) after work' [26]. This is the degree to which employees are able to recover from short term effects of fatigue and distress caused by work activities. The 'NFR after work' scale is a subscale of the Dutch questionnaire on the experience and assessment of work (VBBA) and comprises 11 dichotomous items (yes/no). The scores on the items are summed and transformed into a scale ranging from 0 to 100, with a higher score indicating a higher 'Need For Recovery after work'. The 'NFR after work' scale is a valid and reliable (Cronbach's alpha; 0.88) instrument for measuring 'need for recovery after work' in The Netherlands [26,27,32].

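### The stated inputs (effect size 0.40, two-sided 0.05, 80% power) need 99 to 100 per group, not 63; 63 per group gives about 61% power and is the number for an effect size of 0.50

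*Protocol article*

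**What the plan says.** The Sample size section says that need for recovery after work "is the primary outcome of this study and was therefore used for the power calculation". On the size of effect it states: "Based on previous findings [12,27] the expected effect size is 0.40". The error rate is given as "assuming a two-sided significance level: 0.05", with 80% power. From these inputs it concludes that "63 persons per group are needed". It then inflates for attrition: "Taking into account 20% loss to follow up, the required sample size is 160 persons in total", split equally into 80 and 80.

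The outcome is a score built from 11 yes/no items. The section on the primary outcome says: "The scores on the items are summed and transformed into a scale ranging from 0 to 100". Study design describes a two-armed randomised trial. The calculation is therefore a comparison of two means, expressed as a standardised difference.

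The Sample size section gives no standard deviation, raw difference, correlation between baseline and follow-up, covariate, or gain from repeated measurement. Statistical analyses names linear, logistic and multilevel regression. It ties the multilevel model to the occupational health services, names no baseline covariate, and does not link any of these to the sample size.

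**The concern.** Effect size, significance level, sidedness, power and allocation ratio are all stated, and together they determine the number per group. The stated result is about 36% below what they give ((99 − 63)/99 = 0.36).

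This is the only power statement for the primary outcome. If 63 per group does not deliver 80% power for 0.40, a reader of a null result would take it as fair evidence against an effect of that size, when an unadjusted comparison would miss it about 39% of the time rather than 20%. A null result is a real prospect: Methodological considerations itself warns that a difference on this outcome may be hard to measure. Policy implications ties the findings to uptake by other occupational health settings and to social insurance coverage, so such a misreading would have practical consequences.

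**Working it through.** **Inputs, all from the Sample size section.** Standardised effect d = 0.40; two-sided alpha 0.05 (z = 1.960); power 80% (z = 0.8416); 1:1 allocation; 20% loss.

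**Attempt to reproduce 63.** For two means, n per group = 2(1.960 + 0.8416)² / d².

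- d = 0.40: 2 × 7.849 / 0.16 = 98.1, so 99. The noncentral t-test gives 99.1, so 100.
- d = 0.50: 2 × 7.849 / 0.25 = 62.8, so 63. The t-test gives 63.8, so 64.

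The stated inputs do not return 63. The normal approximation with 0.50 in place of 0.40 does.

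**Loss to follow-up.** 63 / (1 − 0.20) = 78.75, so 79, rounded up to 80. This step is sound, so the fault lies in the 63. Starting from 99 or 100, the same step gives 124 or 125 per group, which is 248 to 250 in total against the stated 160.

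**Power of an unadjusted two-sided t-test at d = 0.40**

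| Evaluable per group | Power at 0.40 | Effect detectable with 80% power |
|---|---|---|
| 63 (stated need) | 60.6% | 0.50 |
| 64 (80 less 20%) | 61.2% | 0.50 |
| 80 (no loss at all) | 71.0% | 0.45 |

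**Other routes to 63 at d = 0.40**

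- One-sided alpha of 0.05 needs 78, and contradicts the stated two-sided test.
- A one-sample or paired test needs 51 to 52, and does not fit a two-arm comparison.
- Adjusting for the baseline score multiplies n by (1 − r²). With r = 0.60, 98.1 × (1 − 0.36) = 62.8. This matches, but r is not in the article.
- Averaging the four follow-ups without baseline adjustment, at a common correlation of 0.5, gives 98.1 × (1 + 3 × 0.5)/4 = 61.3. This is close, but neither the averaging nor the correlation is stated.

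**Power if the analysis did adjust for baseline** (64 per group, d = 0.40, correlations assumed): 74% at r = 0.5, 80% at r = 0.6, 88% at r = 0.7.

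**The case against.** The strongest reply is that the 61% applies only to an unadjusted comparison at one time point. The section names no test, the outcome is measured at baseline and four times afterwards, and regression is planned. Baseline adjustment at a correlation of 0.60 reproduces 62.8 as exactly as an effect size of 0.50 does. An analysis using all four follow-ups with baseline adjustment could have power of about 95% or more at 64 per group (assuming equal correlations of 0.3 to 0.8 between occasions). The article is also a condensed account, and a fuller protocol might hold the missing assumption.

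Part of this stands. The 61% and 39% must be labelled as unadjusted. That the authors used 0.50 is an inference from the numerical match; the text does not say so. The final analysis may well do better than 61%.

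None of it rescues the printed sentence, which presents 63 as following from effect size, alpha and power alone. No unseen document can make that true. If a correlation was used, it is an essential input, and quoting the result without it leaves the claim wrong as written. The Statistical analyses section does not commit to an analysis that would earn the gain.

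It is also fair to say that choosing a correlation of 0.60 merely because it returns 63 would be no repair. Any such value has to come from data.

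**Conclusion.** The concern holds. The stated inputs give 99 to 100 per group, and 63 falls well short. In an unadjusted two-group comparison, 63 to 64 evaluable per group gives about 61% power for 0.40 and reaches 80% only at about 0.50. Full retention of 80 per group would still give only 71%.

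This rests on the section's own figures and on a comparison of two means with equal allocation. It does not depend on which slip produced the 63. The cited basis for 0.40 cannot be checked from the article. The correction is essential because it concerns the power claim for the primary outcome.

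**What to change.** Keep 160 and correct the Sample size paragraph in one of two ways.

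- **(a) No baseline adjustment assumed.** State that 64 evaluable per group gives 80% power for an effect size of 0.50 and about 61% for the expected 0.40, two-sided 5%, unadjusted.
- **(b) Baseline adjustment intended.** State the assumed correlation between baseline and follow-up need for recovery and its data source, and show the calculation: 98.1 × (1 − 0.60²) = 62.8 requires 0.60. Commit the primary analysis to adjust for the baseline score. Give power over a plausible range, for example 74%, 80% and 88% at correlations of 0.5, 0.6 and 0.7. If no source supports about 0.60, use (a).

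The cost is one reworded paragraph plus, under (b), a sentence in Statistical analyses. Under (a) the stated power is less favourable. Neither needs more employees. Holding 80% power at 0.40 without adjustment would instead take 248 to 250 participants, about 90 more than planned.

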### Blinding

Due to the nature of the intervention, it will not be possible to blind the participants, the multidisciplinary team of the VEP integrated care programme, or the OPs of the companies to treatment allocation. After randomization, all participants will receive a non traceable research code consisting of consecutive numbers. A research assistant will enter all data into the computer using these research codes. Thus, the researcher who will analyse the data will be blinded.

### Co-intervention and compliance

Co-interventions cannot be avoided. Information about all treatments and co-interventions received by the participants will be collected by means of questionnaires on health care use in both the intervention and the control group. In the intervention group, the compliance with the recommendations and advices of the VEP integrated care programme will be measured by asking employees which intervention components they received. These recommendations and advices will be compared with the delivered recommendations and advices by the professionals.

### Study groups

#### Intervention group

The participants in the intervention group will be referred to the Audiological Clinic of the VU University Medical Center and receive the VEP integrated care programme.

#### Description of the VEP integrated care programme

The VEP integrated care programme comprises an assessment of auditory function, work demands and personal characteristics by a multidisciplinary team comprising an audiologist, OP, social worker, and psychologist. The VEP integrated care programme is extensively described elsewhere [18] and briefly outlined here.

As soon as an employee is assigned to the VEP integrated care programme, a work-related questionnaire is sent to the employee's home. The employee is asked to fill in the questionnaire and bring it to their consultation at the audiological clinic. This questionnaire assesses the type of work, the work environment, and activities, including hearing activities at work [7].

In the clinic, the hearing status of the employee is measured using auditory tests. Next to regular pure-tone and speech audiometry, SRT tests (presented in quiet and against a background of steady state noise and fluctuating noise) [28,29] are performed. These SRT test aim to measure a person's ability to understand speech in noise by estimating the signal-to-noise ratio (SNR) at which the participant reproduces 50% of the sentences correct. A spatial speech in noise test with interfering speaker is performed to examine hearing in an ecologically valid setting [30]. Furthermore, a loudness scaling test measuring the ability to identify sounds, and a test for localisation [31] are added if indicated.

During a semi-structured interview performed by the psychologist or social worker, the psychosocial status of the employee, and his/her specific needs, attitudes towards hearing loss, work and work-related problems are evaluated. This interview is also attended by the OP of the team to evaluate the (person's perspective on) work-related problems. After the tests and interview, the results are examined and considered by the multidisciplinary team consisting of the psychologist or social worker, the OP, and the audiologist in order to establish an interdisciplinary profile of audiological, personal and occupational characteristics. In a multidisciplinary team meeting, all findings are discussed. A written report is then compiled. This report includes recommendations for the employee and covers a proposed management plan which is discussed by telephone with the OP on site. The request of the OP on site is to supervise the implementation of the recommendations and advices. The participant's general practitioner receives a copy of the written report. Finally, the results and conclusion are discussed with the employee. Possibilities of technical, speech-therapeutic and/or psychosocial interventions are then considered. If indicated, the workplace itself is visited in order to inspect acoustical and occupational circumstances. A schematic figure of the VEP integrated care programme is presented in Figure 2.

**Figure 2 F2:**
[figure not shown]
**Schematic overview of the VEP integrated care programme**.

#### Control group

Participants in the control group will receive usual care, based on advices of their own OP. The OP can refer the employee to the general practitioner, ENT specialist, or to an audiological clinic for further audiological diagnostics and care for hearing impaired persons with work-related difficulties. Furthermore, participant with noise-induced hearing loss will receive care based on existing guidance [16]. Treatment is not restricted in any way but is accurately registered using questionnaires.

### Data collection

Outcome measures will be collected either by online questionnaire or via paper-and-pencil copies. The hard copy questionnaires, including reply paid envelopes, will be sent by regular post to participants without access to or who do not use Internet. Data will be collected at baseline and after 3, 6, 9, and 12 months after baseline measurement. To reduce loss to follow-up, reminders will be sent by e-mail or regular post (paper-and-pencil users) to ask participants to complete the questionnaires with a maximum of three reminders. If they do not wish to further participate in the study, the reasons for their withdrawal will be recorded.

### Outcome measures

#### Primary outcome measure

##### 'Need for recovery after work'

Primary outcome is defined as the 'Need for Recovery (NFR) after work' [26]. This is the degree to which employees are able to recover from short term effects of fatigue and distress caused by work activities. The 'NFR after work' scale is a subscale of the Dutch questionnaire on the experience and assessment of work (VBBA) and comprises 11 dichotomous items (yes/no). The scores on the items are summed and transformed into a scale ranging from 0 to 100, with a higher score indicating a higher 'Need For Recovery after work'. The 'NFR after work' scale is a valid and reliable (Cronbach's alpha; 0.88) instrument for measuring 'need for recovery after work' in The Netherlands [26,27,32].

#### Secondary outcome measures

##### Coping with hearing impairment

The Communication Profile for the Hearing Impaired (CPHI) [33,34] assesses whether a person's communication is effective and whether adequate hearing strategies are used to cope with hearing impairment in daily life. The CPHI reflects an individual's coping-with-hearing-impairment behaviour. The short form of the CPHI with six subscales containing 35 items [33,34] will be used in this study. The six subscales are; 'maladaptive behaviour', 'verbal strategies', 'non-verbal strategies', 'self-acceptance', 'acceptance of loss', and 'stress and withdrawal'. Items are answered on a five-point scale (score 1-5), with either a frequency continuum or an agree- disagree continuum. The item scores of the scales will be recoded such that low scores indicate potential problems. The CPHI is a reliable and valid instrument for application in The Netherlands [33,34].

##### Distress

Distress is measured by the distress scale of the 4DSQ [21]. This scale contains 16 items. The items are scored on a five-point scale using the response categories: 'no', 'sometimes', 'regularly', 'often', and 'very often or constantly'. Every symptom will be recoded into 0 points ('no': symptom is absent); 1 point ('sometimes': doubtfully present); or 2 points ('regularly/often/very often': present at a clinically significant level). Thus, the range of the summed scores is 0-32. Summed scores higher than 10 indicate moderately elevated distress; score higher than 20 indicate strongly elevated distress [21]. The 4DSQ is a reliable and valid instrument for application in The Netherlands [35,36].

##### Health related quality of life

The EuroQol EQ-5D [37] will be used to assess the employees' health related quality of life. The questionnaire describes the respondent's general health status on five domains: 'mobility', 'self-care', 'usual activities', 'pain/discomfort' and 'anxiety/depression', each with three levels (no problems, some problems, and extreme problems). Utilities for the health status will be estimated using the Dutch EQ-5D tariff [38]. Quality-adjusted life years (QALYs) will be calculated by multiplying the utility of a health state with the time spent in this health state. Transitions between health states will be linearly interpolated. Also, the patient's own valuation of his health status will be measured using a Visual Analogue Scale (VAS).

##### Self-efficacy

The General Self-Efficacy Scale (GSES) [39] measures the employees' general beliefs of self-efficacy. Self-efficacy is defined as "the belief of a person in his/her ability to organize and execute behaviours necessary to produce attainments" [39]. It includes 12 items with a five-point response scale from 1 (I totally agree) to 5 (I totally disagree) with sum scores ranging from 12 (most negative) to 60 (most positive) [39]. It is a reliable and valid instrument for use in The Netherlands [39,40].

##### Behavioural determinants

The behavioural determinants attitude, social influence and self-efficacy (ASE) can provide insight into (the intention to perform) the desired behaviour. Questions about attitude, social influence, and self-efficacy for hearing impaired employees are formulated based on questions often used in health promotion research [36,41]. Six questions are included using a five-point response scale from 1 (I totally agree) to 5 (I totally disagree). Sum scores for each behavioural determinant range from 2 (most negative) to 10 (most positive).

##### Sick leave and work productivity

Self reported sick leave days are determined over the past three months using the PROductivity and DISease Questionnaire (PRODISQ). The questions cover relevant aspects of sick leave including compensation mechanisms that may reduce productivity losses at work [42]. Additional data on sick leave and diagnosis are collected from the records of the OHS and Human Resource department of the participating companies after one year follow up to compare the self reported sick leave with the registered sick leave. Self-reported work productivity (i.e., presenteeism) is measured using an item from the WHO health productivity questionnaire [43,44] which asks participants to report their overall work productivity on a ten-point scale in the past three months.

##### Health care use

Health care use is measured using a modified version Tic-P questionnaire [45]. The number of contacts with health care providers specialised in hearing or audiology and all other relevant health care providers (i.e., primary, secondary, psychosocial, and occupational care), the number of medications used, and the number of diagnostic examinations performed during the past three months are included in this questionnaire.

#### Prognostic outcome measure

Psychosocial workload is considered to be a potentially prognostic factor for the primary outcome measure, 'need for recovery after work'. A validated Dutch version of the Job Content Questionnaire (JCQ) [11] will be used to measure the employee's psychosocial work characteristics. Answers are given on a four-point scale, varying from strongly agree to strongly disagree. Scale scores are computed using the job content instrument scale construction formulae [46]. Four subscales are derived from the JCQ: psychological job demands (5 items with a scale score from 12 to 48), physical job demands (5 items with a scale score from 5 to 20), job control (9 items with a scale score of 24-96), and social support (8 items with a scale score from 8 to 32). A higher score indicates a higher psychological job demand, job control, and social support respectively. It is a reliable and valid instrument for application in The Netherlands [11,36,41].

For an overview of the outcome measures and measurement moments see Table 2.

**Table 2 T2:** Schedule of outcome measurements

	T0	T1	T2	T3	T4
**Primary outcome measure - questionnaire**					

'Need For Recovery after work' - NFR after work scale	**×**	**×**	**×**	**×**	**×**

**Secondary outcome measures - questionnaire**					

Coping with hearing impairment - CPHI	**×**	**×**	**×**		**×**

Distress - 4DSQ	**×**		**×**		**×**

Health related quality of life - EQ-5D/VAS	**×**	**×**	**×**	**×**	**×**

Self-efficacy - GSES	**×**		**×**		**×**

Behavioural determinants - ASE	**×**		**×**		**×**

Sick leave - PRODISQ	**×**	**×**	**×**	**×**	**×**

Work productivity - PRODISQ	**×**	**×**	**×**	**×**	**×**

Health care use - Tic-P	**×**	**×**	**×**	**×**	**×**

**Prognostic outcome measure - questionnaire**					

Psychosocial workload - JCQ	**×**		**×**		**×**

Schedule of outcome measurement at baseline (T0), at 3 months (T1), 6 months (T2), 9 months (T3), and 12 months (T4) after baseline measurement

### Costs

A bottom-up cost price calculation will be performed to calculate costs of the intervention and control group. Total costs consisted f costs for the intervention, costs for productivity loss, costs for sick leave, and health care costs. The intervention costs include costs for the implementation of the intervention (i.e., materials and the consultation of the team for the VEP integrated care programme). Costs for productivity loss are costs due to sick leave and costs due to reduced self-reported work productivity. These costs will be calculated according to the human capital cost approach and the friction cost approach, based on income as provided by the employee or as derived from age- and sex-specific income of the Dutch population [47]. The human capital approach assumes that the productivity losses associated with the whole period of sick leave and reduced work productivity. The basic idea of the friction cost approach is that the amount of production lost due to disease depends on the time-span organizations need to restore the initial production level.

Health care costs include costs of the visits to health care providers, diagnostic examinations, and medication due to health problems (i.e., health care problems due to the hearing impairment, but also due to all other complaints). The health care costs will be evaluated according to the prices suggested in the guidelines for economic evaluation in The Netherlands [48]. If cost-guidelines are not available, costs will be estimated using real prices. Medication costs will be valued using prices of the Royal Dutch Society for Pharmacy (Z-index) [49]. All prices are adjusted for the year of 2011 using consumer price index figures.

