### Economic evaluation

In the economic evaluation the costs and consequences of the VEP integrated care programme and usual care will be compared. As mentioned in the introduction, hearing impairment has consequences with potentially substantial costs for the companies, as well for the society. Since interventions in occupational care in The Netherlands have to be paid by employers, the economic evaluation will be conducted from both a company and a societal perspective. From the societal perspective, all costs and consequences of the intervention will be taken into account regardless of who pays for them. From the company perspective, only costs due to the intervention, productivity, and sick leave will be taken into account.

Missing data will be imputed using a multiple imputation procedure according to the multivariate imputation by chained equations (MICE) method [50,51]. To calculate incremental cost-effectiveness ratios (ICER), the difference in mean costs between the intervention and control group will be divided by the difference in outcome measures between the two groups. Confidence intervals (95%) will be estimated using bias corrected and accelerated (BCA) bootstrapping [52]. The cost-effectiveness ratios will be graphically presented in a cost-effectiveness (CE) plane [53]. Cost-effectiveness acceptability curves (CEAC) will also be estimated [54].

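### Summed as listed, total societal costs count sick leave twice, and the company-perspective list is ambiguous on the same point

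*Protocol article*

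**What the plan says.** The Costs section names four components of total costs: "costs for the intervention, costs for productivity loss, costs for sick leave, and health care costs". Later in the same paragraph it defines the second component: "Costs for productivity loss are costs due to sick leave and costs due to reduced self-reported work productivity". It then gives one valuation rule for these costs: "These costs will be calculated according to the human capital cost approach and the friction cost approach". The stand-alone sick-leave item has no definition or valuation of its own.

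Economic evaluation sets two perspectives. The societal one is comprehensive: "From the societal perspective, all costs and consequences of the intervention will be taken into account regardless of who pays for them". The company one is a short list: "From the company perspective, only costs due to the intervention, productivity, and sick leave will be taken into account". For the ICER, "the difference in mean costs between the intervention and control group will be divided by the difference in outcome measures between the two groups".

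Under Sick leave and work productivity, sick days come from one self-report questionnaire. Company records are collected as a comparison with that self-report. Reduced productivity at work (presenteeism) is measured by a separate item, and Table 2 gives the two measures separate rows.

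**The concern.** Sick leave appears both as a component of its own and as part of another component in the same sum. Nothing in the article gives the stand-alone item a different content, such as sick pay or replacement cost, and nothing says it is to be left out when productivity loss is added. An analyst who follows the text costs each day of sick leave twice.

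The economic evaluation is a declared aim of the trial. The Policy implications section links wider use in occupational health care to the company result, and inclusion in the basic social insurance package to the societal result. The background presents sick leave as one of the costs of hearing impairment to companies and society. If its between-arm difference has double weight, the sign of the net cost can change. The cost-effectiveness plane, the bootstrap intervals and the acceptability curves would be built on the same costs.

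**Working it through.** The article states no cost total or ICER, so there is no figure to reproduce. The check is algebra on its own definitions.

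**Notation.** Costs per person: I = intervention, S = sick leave, P = reduced productivity at work, H = health care. D before a letter is the difference in means, programme minus usual care.

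**Societal perspective** (component list and definition from Costs; all costs included, from Economic evaluation)

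- As listed: I + (S + P) + S + H = I + 2S + P + H
- Sick leave once: I + S + P + H
- Excess in the ICER numerator: (DI + 2DS + DP + DH) − (DI + DS + DP + DH) = DS

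**Company perspective** (list from Economic evaluation), two readings

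- Productivity as defined in Costs: DI + (DS + DP) + DS = DI + 2DS + DP, excess DS
- Productivity as presenteeism only: DI + DP + DS, excess 0

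**When the sign changes.** Let K be the sum of all the other differences (societal: DI + DP + DH; company: DI + DP). Counted once, the net difference is K + DS; counted twice, it is K + 2DS. The two have opposite signs when DS lies between −K and −K/2.

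**Illustration.** All figures are assumed and none is in the article: DI = +1,000, DP = 0, DH = 0, in EUR per person, so K = 1,000.

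| DS | As listed (1,000 + 2DS) | Counted once (1,000 + DS) | Excess |
|---|---|---|---|
| −1,500 | −2,000 | −500 | −1,500 |
| −1,000 | −1,000 | 0 | −1,000 |
| −750 | −500 | +250 | −750 |
| −500 | 0 | +500 | −500 |
| 0 | +1,000 | +1,000 | 0 |
| +500 | +2,000 | +1,500 | +500 |
| +1,000 | +3,000 | +2,000 | +1,000 |

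With these inputs the sign is reversed for DS between −1,000 and −500. Outside that range the size is wrong but the direction is not. Setting DP = −500 instead of 0 lowers both columns by 500 and leaves the excess unchanged.

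**Spread.** Because Var(2S) = 4 Var(S), double entry also changes the variance of total costs. The intervals and acceptability curves can therefore be affected even where DS is zero.

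**The case against.** The strongest reply is that the separate sick-leave entry is a redundant item in a list and not an analysis rule. One valuation rule covers sick leave and reduced productivity together, and there is one self-reported quantity of sick leave, so a health economist would probably count it once. This is plausible, and it is why the point has to be conditional: sick leave would be counted twice if the components are summed as listed. It does not remove the point, because the two statements conflict within one paragraph and nothing in the article says which governs.

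A reader might infer that the company perspective is certainly wrong too. The documents do not support that. Its list reads "only costs due to the intervention, productivity, and sick leave will be taken into account". It does not use the defined term productivity loss, and the outcome section and Table 2 keep work productivity apart from sick leave. On that usage sick leave is counted once. The wording is ambiguous there, not shown to be in error.

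A reader might also infer a second overlap, in the programme arm only: team consultations are costed as intervention, while the health care questionnaire covers "The number of contacts with health care providers specialised in hearing or audiology and all other relevant health care providers". This is not established. The questionnaire is a modified version whose items and instructions are not shown, and excluding study visits is a detail that an article commonly leaves to the full protocol. Removing the programme's auditory tests from health care costs could even leave them uncosted, since intervention costs are described only as materials and team consultation. This inference is not part of the point.

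Finally, the primary outcome is need for recovery. Its analysis, the sample size and the data collection are unaffected.

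**Conclusion.** The inconsistency within the Costs section is real. Applied as written, it gives sick leave a weight of two in the societal total and shifts the ICER numerator by DS, the between-arm difference in mean sick-leave cost. The direction follows the sign of DS, and the shift is zero only if DS is zero. The company perspective has the same shift under one reading of its list and none under the other.

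The size in euros cannot be derived from the article. The table shows only what is possible under assumed inputs, with differences in presenteeism and health care cost set to zero. The conclusion rests on the stand-alone item meaning the same sick leave as the one inside productivity loss; the article gives it no other meaning.

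**What to change.** In Costs, define total costs = intervention + absenteeism (sick leave, counted once) + presenteeism (reduced self-reported productivity at work) + health care. In Economic evaluation, define the company perspective = intervention + absenteeism + presenteeism. Use these same terms in both sections, and drop productivity loss as a component or keep it only as the label for absenteeism plus presenteeism together.

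This is a change of about two sentences. It needs no new data and leaves the planned valuation methods as they are. It should be settled before the cost data are analysed, so that the choice between two cost totals is not made with results in view.
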